### Analysis Plan

Statistical analyses will be performed using SPSS version 20 (SPSS, Inc.). All statistical tests will be considered significant at *P* less than .05.

### Baseline Questionnaire

Patient demographics and baseline variables will be characterized with descriptive statistics, using mean with standard deviation and number with frequency for continuous and categorical variables, respectively.

### Clinical Performance

Clinical performance during the live colonoscopies for each group will be determined by comparing the scores from the DOPS, GiECAT, NAPCOMS, and Modified-OSANTS. Specifically, a mixed factor 2 (control curriculum versus intervention curriculum) times 2 (procedure 1 versus procedure 2) analysis of variance (ANOVA) will be used to determine whether there is a difference based on the rating scales. The Tukey honest significant difference (HSD) test will be used as a post-hoc analysis to determine any significant differences.

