### Experimental Design

#### Baseline Questionnaire

A written questionnaire is administered to all participants at the start of the training to collect demographic and background information including age, sex, level of training, previous endoscopy experience, and nature of experience (if applicable). Previous experience with team sports and video games is also assessed, as these activities correlate with NTS and baseline endoscopic skill, respectively (Multimedia Appendix 1) [10].

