#### Pre-Test

Participants take part in a pre-test designed to assess their baseline (1) knowledge of colonoscopy (knowledge test); (2) technical skills (VR simulation test); and (3) NTS (VR simulation-based “integrated scenario” test). No feedback is provided at any point during the pre-test.

The knowledge test is a 30-minute test containing 20 multiple choice questions (MCQ) designed to assess participants’ theoretical knowledge of colonoscopy, including indications, sedation, safety, findings, pathology, and follow-up (Multimedia Appendix 2).

Participants' baseline endoscopic technical proficiency is assessed through the completion of a colonoscopy procedure on the VR simulator (EndoVR Colonoscopy Module 3). This scenario simulates a screening colonoscopy, without the need for any type of intervention, such as biopsy. There is a time limit of 30 minutes per procedure. An expert rater assesses performance, but does not provide assistance. Participants are videotaped to obtain performance measures with their faces hidden to ensure anonymity. Prior to starting the procedure, participants complete a questionnaire to measure their self-efficacy.

Following the simulator-only test, participants complete an integrated scenario format test to assess their baseline endoscopic non-technical proficiency. The integrated scenario requires participants to perform a colonoscopy procedure on the VR simulator while interacting with an endoscopic nurse and a standardized patient (SP) [11]. The simulated procedure mimics the setup of an endoscopic suite with the VR simulator positioned next to a patient table. An SP, who receives instructions regarding their medical role, acts out a scenario on colon cancer screening. Trainees are expected to explain the colonoscopy procedure, its benefits and risks, and obtain procedural consent. Trainees then carry out the procedure on the VR simulator (EndoVR Polypectomy Module #3) while responding to the patient and interacting with the standardized nurse (SN), as appropriate. The SP acts out cues from the VR simulator when the simulator signals that the procedure has exceeded its threshold for discomfort. The performances of all participants are videotaped in a similar manner to the VR simulation test to obtain performance measures. Participants are given a maximum of 45 minutes to complete the procedure. Prior to starting the procedure, participants complete a questionnaire to measure their self-efficacy.

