#### Training Intervention

Participants are subsequently randomized using a randomization algorithm to 1 of 2 groups (control and intervention), following a 1:1 allocation distribution.

The control group receives 4 hours of interactive, small-group, didactic and hands-on sessions on the theory of colonoscopy, led by an expert academic gastroenterologist. The core curriculum was designed based on the American Society for Gastrointestinal Endoscopy (ASGE) colonoscopy curriculum and a detailed endoscopic training textbook and includes teaching on anatomy, pathophysiology, indications, risks and benefits of the procedures, training on specific elements of performance of colonoscopy procedures (eg, one-handed steering), and strategies for loop reduction, terminal ileal cannulation, and adequate visualization of mucosa [12,13]. This curriculum has been shown to be effective when compared to self-regulated learning on the simulator [3]. The sessions are interlaced with 6 hours of expert-assisted instruction on both the low-fidelity simulator (1 hour) and on the high-fidelity VR simulator (5 hours). Six modules of increasing difficulty in colonoscopy and colonoscopy polypectomy are taught with one-on-one feedback from an expert academic endoscopist. The endoscopy instructor demonstrates techniques, answers questions, and provides individualized performance feedback on global performance. The final 2 hours spent on the high-fidelity scenario use the integrated scenario, which features an SP and SN.

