### Outcome Measures

The primary outcome measure is the difference in performance between the control and intervention groups during participants’ 2 clinical colonoscopies. Each videotaped clinical colonoscopy will be independently assessed by 2 experienced endoscopists using the Joint Advisory Group for GI Endoscopy Direction Observation of Procedural Skills (JAG DOPS) (Multimedia Appendix 4) [15]. The raters will be blinded to the group assignment. Training on how to use the tool will be provided for raters by the investigators of the study.

Secondary outcome measures include the differences between the control and intervention groups with respect to (1) procedural knowledge, as assessed by the knowledge MCQ tests; (2) NTS performance during the clinical colonoscopies, as assessed by the Modified Objective Structured Assessment of Non-Technical Skills (M-OSANTS) for colonoscopy, which has been previously validated for surgery and modified for endoscopy [4] (Multimedia Appendix 5); (3) clinical performance on clinical colonoscopies, as assessed by the Gastrointestinal Endoscopy Competency Assessment Tool (GiECAT) [16] (Multimedia Appendix 6); (4) technical performance on a VR simulated colonoscopy after training and 4 to 6 weeks after training (immediate and delayed post-training assessments, respectively), as assessed by the JAG DOPS and the GiECAT; (5) technical and non-technical performance during an integrated scenario format test 4 to 6 weeks after training, as assessed by the JAG DOPS, GiECAT, and M-OSANTS; (6) patient comfort during the clinical colonoscopies, as assessed by the Nurse-Assessed Patient Comfort Score (NAPCOMS) [17] (Multimedia Appendix 7); (7) participant self-efficacy, as measured by an adapted scale based on the General Self-Efficacy Scale (GSE) [18,19] (Multimedia Appendix 8); and (8) global performance and communication skills during integrated scenarios as assessed by the Integrated Scenario Global Rating Form (ISGRF) and Integrated Scenario Communication Rating Form (ISCRF) [11,20,21], respectively (Multimedia Appendices 9 and ).

Experienced endoscopists will assess participants’ colonoscopy-specific skills, technical skills, and NTS during the pre-training, immediate, and delayed post-training simulation-based assessments.

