#### Technical Performance

Technical performance on the simulator for each group will be determined by comparing the scores from the DOPS and GiECAT. Specifically, a mixed factor 2 (control curriculum versus intervention curriculum) times 3 (pre-test, post-test, delayed test) ANOVA will be used to determine whether there is a difference based on the rating scales. The Tukey HSD test will be used as a post-hoc analysis to determine any significant differences.

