**Previous endoscopic experience, mean (SD)**			
	Number of independent colonoscopies	0.11 (0.46)	0.30 (0.82)
	Number of assisted colonoscopies	2.63 (4.66)	1.70 (2.50)

^a^NTS: non-technical skills.

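### The primary ANOVA of clinical DOPS is valid but leaves out the pre-randomisation simulator DOPS score, a nearly free covariate that could sharpen the arm comparison

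*Protocol article*

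**What the plan says.** Under Outcome Measures: "The primary outcome measure is the difference in performance between the control and intervention groups during participants’ 2 clinical colonoscopies", rated with the JAG DOPS by two blinded endoscopists.

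Under Clinical Performance, the analysis of DOPS, GiECAT, NAPCOMS and M-OSANTS is fixed: "a mixed factor 2 (control curriculum versus intervention curriculum) times 2 (procedure 1 versus procedure 2) analysis of variance (ANOVA) will be used". No baseline term is named.

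A baseline on the same instrument is planned. Under Pre-Test: "Participants' baseline endoscopic technical proficiency is assessed through the completion of a colonoscopy procedure on the VR simulator". Outcome Measures adds: "Experienced endoscopists will assess participants’ colonoscopy-specific skills, technical skills, and NTS during the pre-training, immediate, and delayed post-training simulation-based assessments". The Training Intervention section puts allocation after this step: "Participants are subsequently randomized using a randomization algorithm to 1 of 2 groups (control and intervention), following a 1:1 allocation distribution". No stratification is described.

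The pre-test scores have a planned use, but only for the simulator outcomes. For simulator DOPS and GiECAT, the Technical Performance section says "a mixed factor 2 (control curriculum versus intervention curriculum) times 3 (pre-test, post-test, delayed test) ANOVA will be used", and the Non-Technical Performance section uses the same layout for M-OSANTS. Results reports that all 42 participants completed the study, 19 in the control group and 23 in the NTS group.

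**The concern.** The curriculum effect is a comparison between participants. Stable differences in skill between trainees therefore sit in the error term of the one test that answers the trial's question. A second procedure per trainee averages out variation between procedures, but it does not remove differences between trainees. A baseline measure of skill can remove part of them.

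With 42 people and no described stratification, the arms may also differ somewhat in starting skill by chance. An unadjusted contrast carries that difference; an adjusted one corrects for the part the covariate captures.

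At stake are efficiency and the estimate conditional on the allocation that occurred. Validity is not in question. The point is worth making because the covariate is already in the data-collection plan and the article describes rating and analysis as unfinished.

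**Working it through.** **Inputs from the Protocol article.** 19 and 23 participants, no losses (Results); two clinical procedures each (Delayed Testing); f=0.65, two-sided alpha .05, beta .20, 2 groups, 3 measurements, 16 participants required (Sample Size Estimation).

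**Assumptions.** The correlation rho between repeated measurements and the correlation r between pre-test simulator DOPS and a participant's mean clinical DOPS are not given, so ranges are shown. Each participant is taken to have both clinical procedures and a pre-test score.

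**1. The plan's own figure.** For the between-group factor, lambda = f²·N·m/(1+(m−1)·rho), with df = (1, N−2). At rho=0.5, N=16, m=3: lambda = 0.4225×16×3/2 = 10.14 and power is 0.841. The stated 16 reproduces.

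**2. Planned effect in the primary model.** That model has two measurements, so m=2 and N=42. At rho=1, lambda = 0.4225×42 = 17.7 and power is 0.984 (0.983 with the 19/23 split). At rho=0.3, lambda = 0.4225×84/1.3 = 27.3 and power is 0.999. Unadjusted power at f=0.65 is therefore at least about 98%.

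**3. Detectable difference, unadjusted.** With complete data, the arm test in the 2×2 mixed ANOVA is the t-test of participant means.
- SE in SDs of the participant mean = √(1/19+1/23) = 0.310, on 40 df.
- The noncentral t gives 80% power at 0.89 SD.

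**4. Detectable difference with one covariate.**
- Residual variance is multiplied by (1−r²).
- One df is lost (39 remain).
- Estimating the slope inflates the variance by about 1+1/38 = 1.026.
- At r=0 the detectable difference is 0.902 SD. At other values it is 0.902×√(1−r²).

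| r | √(1−r²) | Detectable difference at 80% power | Power at 0.89 SD | Power at 0.8 SD |
|---|---|---|---|---|
| unadjusted | – | 0.89 | 80.0% | 71% |
| 0 | 1.000 | 0.90 | 78.9% | 70% |
| 0.2 | 0.980 | 0.88 | 80.5% | 72% |
| 0.3 | 0.954 | 0.86 | 82.6% | 74% |
| 0.5 | 0.866 | 0.78 | 89.1% | 82% |
| 0.6 | 0.800 | 0.72 | 93.2% | 87% |

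Adjusted and unadjusted power are equal at r of about 0.16. Below that, adjustment costs at most about 1 point.

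**5. Gain at the planned effect.** At d = 2×0.65 = 1.3 (the rho=1 case), power is 98.3% unadjusted, 98.8% at r=0.3 and 99.7% at r=0.5. The gain there is negligible.

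**6. Chance imbalance.** The SD of a standardised baseline difference between arms of 19 and 23 is also 0.310. As an illustration, a gap of 0.3 SD in pre-test skill with r=0.5 moves the unadjusted contrast by 0.3×0.5 = 0.15 SD. That is 0.15/0.310, or about half a standard error.

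**The case against.** The strongest reply is that nothing in the plan is wrong. Under 1:1 randomisation the group-by-procedure ANOVA is unbiased with the correct type I error, and no stated figure fails. That stands: a reader might infer that the primary test is invalid or biased, and the article does not support this.

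Second, the benefit rests on an unstated r, and the article gives reasons why it could be low. The pre-test is a single unassisted simulator case performed by near-beginners, whose scores may bunch near the floor. The outcome comes weeks after training, on real patients, with an attending who may help or take over. This also stands, which is why the range starts at r=0. The balance still favours adjusting: about 1 point of power at risk against 3 points or more from r=0.3 upward, at effects near 0.8 to 0.9 SD.

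Third, power at the planned effect is already about 98%, so the article does not show an underpowered trial. That effect came from a surgical NTS curriculum, however. Here the arms differ in one didactic hour, a checklist and the focus of feedback, so a smaller effect is possible.

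Fourth, a reader might take Table 1 as proof of an imbalance that must be corrected. It is not. "Number of assisted colonoscopies" is higher in control (2.63 versus 1.70), but independent colonoscopies are higher in the NTS group (0.11 versus 0.30). The standardised differences are about 0.25 and 0.29, in opposite directions and within one chance SD of 0.31. Age differs more (29.5 versus 28.1), but the article links it to no outcome and this covariate would not address it. Pre-test DOPS is not reported by arm, so no imbalance in it is shown. Table 1 therefore supports neither the claim nor prior experience as a covariate.

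Finally, a supportive adjusted analysis could sit in an analysis plan not shown. That is possible, but the article sets out the clinical model factor by factor and uses the pre-test as a level only in the simulator models. The comment concerns that stated choice.

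**Conclusion.** The point holds as a worthwhile improvement, not as an error. The primary model omits a pre-randomisation score on the primary instrument that is planned for every participant.

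Including it would change the difference detectable at 80% power from 0.89 SD to between 0.90 (r=0) and 0.72 (r=0.6). At a true effect of 0.8 SD, power would rise from 71% to 82% if r=0.5. These figures assume complete data, one covariate and a linear relation; r is an assumption throughout. If r is below about 0.16, or the true effect is as large as planned, there is nothing material to gain and at most about 1 point of power to lose.

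**What to change.** Before scores are unblinded, prespecify the primary analysis as an ANCOVA or linear mixed model of clinical DOPS on arm and procedure, with pre-test simulator DOPS as the single covariate. Use pre-test GiECAT and pre-test integrated-scenario M-OSANTS in the same way for those clinical outcomes. Retain the planned unadjusted 2×2 ANOVA as a sensitivity analysis, and date the change so that the covariate cannot appear to have been chosen from the results. Because performances are scored from video, confirm that pre-test recordings are rated without knowledge of arm.

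The cost is one degree of freedom, a small slope-estimation penalty and a change of wording. No new data are needed.

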### Sample Size Estimation

A power analysis was computed using G*Power version 3.1.9 [22]. Using a previous study that evaluated an NTS training curriculum in surgery, we conducted the analysis using the relevant effect size [4]. Based on an effect size of f=0.65, an alpha of .05 (2-tailed), a beta of .20, 2 groups, and 3 measurements, 16 participants are required to achieve a power of greater than 0.80 using repeated measures ANOVA (between-factors). Furthermore, a previous study comparing a curriculum in endoscopic simulation found that a minimum of 15 participants per group was sufficient to detect a significant difference [3]. To accommodate for a projected 20% dropout and/or non-response, we recruited a total of 42 participants.

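### Tukey HSD, named after all four mixed ANOVAs, adds nothing for two-level factors and has no fixed error rate for comparing the arms at a given occasion

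*Protocol article*

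**What the plan says.** The Clinical Performance section, which covers the primary DOPS outcome, sets out a mixed ANOVA with two curricula (between participants) and two procedures (within participants). It then adds: "The Tukey honest significant difference (HSD) test will be used as a post-hoc analysis to determine any significant differences".

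The Technical Performance, Non-Technical Performance and Self-Efficacy sections each specify "a mixed factor 2 (control curriculum versus intervention curriculum) times 3 (pre-test, post-test, delayed test) ANOVA", and each ends with the same instruction: "The Tukey HSD test will be used as a post-hoc analysis to determine any significant differences". Under Analysis Plan: "All statistical tests will be considered significant at" a P value below .05.

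None of the four sections says which means HSD compares (groups, occasions or group-by-occasion cells), which error term it uses, or whether it runs only after a significant F test. Outcome Measures defines the primary and secondary outcomes as differences between the control and intervention groups. For simulator technical performance it names the immediate and delayed assessments, and for one of the integrated-scenario outcomes the delayed assessment.

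**The concern.** Tukey's procedure is built for all pairwise comparisons among three or more independent means that share one error variance. The group factor has two levels everywhere, and so does procedure in the clinical analysis. There the F test already is the only pairwise comparison.

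HSD has work to do on an arm question only if it is run over the four cells of the 2×2 or the six cells of the 2×3. Each participant contributes to two or three of those cells, so they are correlated. A between-arm difference at one occasion carries the full between-participant variance, while a within-arm change does not. One error term cannot suit both. Depending on the term used, occasion-specific arm differences could be declared too often, or real ones missed, at a nominal 5% level.

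**Working it through.** **Inputs.** From the article: 2 groups; 2 procedures or 3 test times; 19 control and 23 intervention participants (Results); level .05 (Analysis Plan). Assumed, because the article gives none: normal scores with equal variances, and the same correlation ρ between any two occasions, taken as 0.3, 0.5 and 0.7.

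**The plan's own figure.** There is none for the post-hoc step. The nearest is the sample size of 16, described as sufficient "to achieve a power of greater than 0.80 using repeated measures ANOVA (between-factors"). With f = 0.65, m = 3 and assumed ρ = 0.5, the noncentrality is λ = f²Nm/(1+(m−1)ρ) = 0.4225×16×3/2 = 10.14. On 1 and 14 df this gives power 0.841, so 16 reproduces. That calculation concerns the between-group effect; it neither uses nor supports HSD.

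**Two-level factors.** HSD rejects when |t| > q/√2. With 40 error df, q(2,40)/√2 = 2.0211, and t(0.975,40) = 2.0211. The two tests are identical.

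**Arm comparison at one occasion, within-participant error.** The variance of the difference is σ²(1/19+1/23), but the within-participant mean square estimates σ²(1−ρ). The HSD cut-off is therefore effectively multiplied by √(1−ρ):

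| | Nominal cut-off q/√2 | ρ=0.3 | ρ=0.5 | ρ=0.7 |
|---|---|---|---|---|
| 2×2 (4 cells, 40 df) | 2.680 | 2.24 | 1.90 | 1.47 |
| 2×3 (6 cells, 80 df) | 2.920 | 2.44 | 2.06 | 1.60 |

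An unadjusted two-sided 5% test on 40 df needs 2.02. In the 2×2 the supposedly adjusted criterion is already looser than that at ρ = 0.5.

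**Simulated error rates** (20,000 null trials per correlation; HSD run regardless of the F tests):

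| False between-arm differences | ρ=0.3 | ρ=0.5 | ρ=0.7 |
|---|---|---|---|
| 2×2, any between-arm pair, within-participant error | 8.8% | 16.1% | 29.0% |
| 2×2, same-procedure pairs only, within-participant error | 5.9% | 11.8% | 23.4% |
| 2×2, any between-arm pair, pooled error | 3.2% | 3.1% | 2.7% |
| 2×3, same-time pairs, within-participant error | 4.8% | 10.5% | 23.3% |
| 2×3, same-time pairs, pooled error | about 1.3% | about 1.3% | about 1.3% |

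Repeat runs agreed to within about one percentage point.

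**HSD used only as a follow-up** (2×2, any between-arm pair, within-participant error): after a significant group F test, 3.6% / 4.6% / 5.1%; after a significant group or interaction F test, 5.2% / 6.9% / 7.9%.

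**HSD on the three time means, averaged over arms.** With the within-participant error term, familywise error is 4.8% to 5.2% under equal correlations and 5.4% to 5.9% in two non-spherical patterns tried. In those patterns the error is unevenly spread, with single pairs at 0.03% to 4.0% against about 1.9% under sphericity. If the times are treated as independent, the rate falls to 1.5% / 0.4% / 0.02% at ρ = 0.3 / 0.5 / 0.7.

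**The case against.** The strongest reply is that HSD is only a follow-up. The Clinical Performance section assigns the question of whether there is a difference to the ANOVA, and the group F test there holds its size at about 5%. On the group factor HSD gives the same answer, so it does no harm. The largest error rates need three things the article does not state: HSD over all cells, the within-participant error term for between-arm pairs, and no preceding F test. The 2×2 figures of 9% to 29% also count cross-procedure pairs. A condensed article may properly leave contrasts and error terms to a fuller plan.

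Much of this stands, and it rules out three stronger readings.

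- A reader might infer that the primary analysis is invalid, or that HSD could overturn a significant group effect. The text gives HSD no such authority.
- A reader might infer that HSD is invalid for any repeated measure. On the three time means, with the within-participant error and sphericity, it is acceptable.
- A reader might take 29% as the trial's error rate. It is one corner of an assumed range.

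The reply does not remove the point. The article names a specific procedure four times, so this is a stated choice and not just an omitted detail. No fuller document could make HSD informative for a two-level factor. The use in which HSD behaves well compares times averaged over arms, whereas Outcome Measures asks about differences between arms.

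**Conclusion.** The point holds in a limited form. HSD is redundant for group in all four analyses and for procedure in the clinical one; this follows from the design and needs no assumption. For arm comparisons at a given occasion it is unsuitable, because its error rate depends on an error term the article does not state. Under equal correlations of 0.3 to 0.7 and ungated use, the within-participant term gives about 9% to 30% for any between-arm pair in the 2×2 and 5% to 23% for same-time pairs in the 2×3. A pooled term gives about 1% to 3%. At a correlation of 0.3 there is no inflation for same-time pairs in the 2×3, and gating on the group effect keeps the 2×2 rate near 5% or below.

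The primary group main-effect test is unaffected. What needs correcting is the follow-up step and the secondary arm comparisons that rely on it.

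**What to change.** **Clinical Performance (2×2).** Delete the HSD sentence. State that the primary test is the group main effect on DOPS, taken as the mean of the two procedures, reported as a between-arm difference with its 95% CI.

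**Technical Performance, Non-Technical Performance and Self-Efficacy (2×3).** Replace the HSD sentence with pre-specified arm contrasts at post-test and at delayed test, using the between-participant standard error appropriate to each. Adjust over the two times; Holm is one suitable choice among several. If within-arm change is to be reported, use paired contrasts with a multiplicity adjustment. Bonferroni-adjusted paired tests over the three times held 4.0% to 4.7% in the same simulations, including the non-spherical patterns.

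**Cost.** One sentence changes in each of four sections. No new data are needed, and the article reports that assessment and analysis were still under way, so the change could be made before results were known.
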